### Statistical analysis

We will estimate the mean treatment effect of MBT relative to UC on the primary outcome (CBCL) as well as each of the secondary outcomes (Parental Well-Being, Stress, and Reflective Functioning, SDQ, Kidscreen, SSAP, and Parental Mind-Mindedness) at T2 and T3 separately, but using the same method each time, as follows.

Treatment assignment will be stratified into municipalities, and within each stratum, it will be assigned to clusters based on foster care consultants. Hence the estimation needs to account for both the stratification and the clustering. We will thus use linear regression for T2 and T3 outcomes separately, in each case controlling for pre-treatment outcomes. Within each stratum, we will then use linear regression, estimating robust clustering standard errors in order to account for the potential correlation between subjects assigned to the same consultant. Using the strata-specific treatment effects, we will then compute the mean treatment effect as the weighted mean of the within-stratum estimates weighted by stratum share. We can calculate the variance by averaging the within-stratum cluster robust variance, weighted by stratum share squared [70]. All analyses will use a significance level of 0.05.

Analyses will be based on the intention-to-treat (ITT) principle, analyzing each subject as part of the treatment to which they were originally assigned, regardless of whether treatment was in fact received.

If there is substantial attrition in outcome data collection, this will potentially introduce selection bias in the estimated effect if attrition selection is on unobservables. While doing so does not solve the problem of attrition selection on unobservables, we will follow the standard in the literature and analyze sensitivity by handling missing values using multiple imputation using all baseline variables.

Further, we will perform subgroup analysis in order to examine whether treatment effects differ across subgroups based on age (4–9 and10–17 years), number of previous foster care placements, municipality budget per capita (low or high) as well as parental background variables.

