### Power considerations

Based on previous research, we expect an effect size of *d* = 0.53 for children’s overall psychosocial adjustment [40]. Based on 23 foster care consultants in each group, a power of 0.80, a type 1 error rate of 0.05, and an intra-class correlation (ICC) of 0.1, we need to include 3 families for each foster care consultant in the study (a total of 138 families). We aim to recruit 175 families (3.8 for each foster care consultant) to leave room for drop-out and allow power to conduct moderator analyses.

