Other potential limitations relate to methodological as well as practical challenges. A practical challenge concerns the probability of attrition among foster families allocated to the control group. If MBT is perceived as an attractive offer, being assigned to UC while still spending time answering questionnaires and providing a video of foster parent/child interaction to be used for research might be difficult to accept. Because we cannot apply strict random allocation, comparability between the intervention group and control group cannot be guaranteed, and conclusions about causality are expected to be tentative rather than definitive. On the other hand, the study is conducted in a naturalistic setting, which can be regarded as a strength as it increases the ecological validity of our findings and the likelihood that the municipalities may decide to continue to offer the MBT intervention after the end of the trial.

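### The protocol names attrition on unobservables as a source of bias, but the one sensitivity analysis it states assumes that mechanism away and cannot show how far it could move the CBCL result

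*Protocol article*

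**What the plan says.** In the protocol article, the Statistical analysis section estimates the MBT effect at T2 and T3 separately. It uses linear regression controlling for the pre-treatment outcome, within municipality, with cluster-robust standard errors. On missing outcomes it begins "If there is substantial attrition in outcome data collection" and continues "this will potentially introduce selection bias in the estimated effect if attrition selection is on unobservables". The response is multiple imputation using all baseline variables, introduced with "While doing so does not solve the problem of attrition selection on unobservables, we will follow the standard in the literature". The article states no other missing-data analysis.

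The Discussion says where loss might arise: "A practical challenge concerns the probability of attrition among foster families allocated to the control group". The reason given is that MBT may look attractive, so that usual care plus questionnaires and video may be hard to accept.

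Power considerations gives no dropout rate. It says only "We aim to recruit 175 families (3.8 for each foster care consultant) to leave room for drop-out", and adds that the surplus also serves moderator analyses.

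**The concern.** A sensitivity analysis is useful when it relaxes the assumption in doubt. Here that assumption is that families without T2 or T3 data have the outcomes one would predict from their arm and baseline data. The article does not say how the main regression treats missing outcomes. Since imputation is the sensitivity analysis, the main regression presumably uses families with data, and it then needs this assumption. Imputation from baseline variables needs it too, though it conditions on more of them. The two results can agree closely while both are biased in the same direction.

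The trial's setting makes the question worth asking. Families know their allocation before they consent (Recruitment), they are not blinded (Blinding), and the foster parent rates the CBCL (Primary outcome). If families leave because of how the child fares after baseline, no baseline variable captures that. The trial could then report its primary result without any indication of how much outcome-dependent dropout the result would withstand, in either direction.

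**Working it through.** **1. The plan's own figure.** Inputs from Power considerations: d = 0.53, 23 consultants per arm, power 0.80, type 1 error 0.05 (taken as two-sided), ICC 0.1.

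- Per arm without clustering: 2 × ((1.960 + 0.842)/0.53)² = 55.9, so 56.
- Design effect with 3 families per consultant: 1 + (3 − 1) × 0.1 = 1.2, and 56 × 1.2 = 67.2.
- Families per consultant: 67.2/23 = 2.92, so 3, and 46 × 3 = 138. The stated 138 is reproduced.
- Room for loss: 1 − 138/175 = 21.1%. This is an upper reading, not a stated dropout allowance, because part of the surplus is for moderator analyses.

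**2. Formula for the shift.** Let p be the share missing in an arm and δ the amount, in SD, by which the true mean of the missing children departs from the imputed mean. The MBT minus UC contrast is then wrong by

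p(MBT) × δ(MBT) − p(UC) × δ(UC).

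A low CBCL score is good. If control leavers in fact did better than imputed, the benefit of MBT is overstated. If they did worse, it is understated.

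**3. Illustration.** Neither p nor δ is in the document. Assume 25% missing in UC and 10% in MBT. With equal arms this is 17.5% overall, within the 21.1%.

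| Departure | Where it applies | Size of shift (SD) | Share of 0.53 |
|---|---|---|---|
| 0.3 SD | both arms, same direction | 0.25 × 0.3 − 0.10 × 0.3 = 0.045 | 8% |
| 0.3 SD | UC only | 0.25 × 0.3 = 0.075 | 14% |
| 0.5 SD | both arms, same direction | 0.25 × 0.5 − 0.10 × 0.5 = 0.075 | 14% |
| 0.5 SD | UC only | 0.25 × 0.5 = 0.125 | 24% |

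**4. Would the conclusion change?** Start from 87.5 families per arm.

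- UC after loss: 87.5 × 0.75 = 65.6 families, or 2.85 per consultant, design effect 1.185.
- MBT after loss: 87.5 × 0.90 = 78.75 families, or 3.42 per consultant, design effect 1.242.
- SE = √(1.185/65.6 + 1.242/78.75) = 0.184. This ignores any gain from baseline adjustment and any added imputation variance.
- Smallest significant estimate: 1.96 × 0.184 = 0.361.
- Observed 0.53, largest shift in the table: 0.53 − 0.125 = 0.405, and 0.405/0.184 = 2.2. Still significant.
- Observed effects from 0.361 up to 0.361 + 0.045 = 0.406 would lose significance under the smallest shift, and up to 0.361 + 0.125 = 0.486 under the largest.

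**5. Outside that range.** At 25%/10% loss, an observed 0.53 loses significance only once control leavers alone depart by (0.53 − 0.361)/0.25 = 0.68 SD. On the same basis the threshold is about 0.78 SD at 21%/21% loss, 0.55 SD at 30%/10% and 0.38 SD at 40%/10%. If the arms depart by 0.5 SD in opposite directions at 25%/10%, the shift is 0.125 + 0.05 = 0.175. The estimate is then 0.355 and 0.355/0.184 = 1.93, just short of significance.

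**The case against.** The strongest reply is that the article says nothing false. It names the problem, plans a common analysis and states that analysis's limit openly. A not-at-random analysis may be in a statistical analysis plan that is not shown. That is fair as far as it goes: the point holds for this article only. Still, the article is not silent. It fixes a sensitivity analysis and concedes that this does not reach the threat just named. The concession should discourage over-reading, but it does not tell a reader how large the bias could be. The Discussion's caution that causal conclusions will be tentative is attributed to the lack of strict random allocation, not to attrition.

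Three further objections stand and limit the point.

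- A reader might infer that the protocol predicts outcome-dependent dropout in the control arm. It does not. The Discussion speaks of a probability of attrition and ties it to disappointment with allocation. Dropout that depends on arm and baseline CBCL alone is compatible with missing at random.
- A reader might infer that imputation is run only if overall attrition is substantial. The word overall is not there. The condition can be read as attached to the statement about bias rather than to the imputation. The text is ambiguous, and substantial has no threshold.
- The inputs to the illustration are assumptions, and the article plans measures to limit loss: researcher contact (Usual care), and reminders, help with questionnaires and gift cards (Data collection). These reduce attrition but do not show what the remainder could do.

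Richer imputation, for example using T2 scores when imputing T3, would make missing at random more plausible. It would still rest on that assumption.

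**Conclusion.** The point holds as a mismatch between the threat the article states and the check it states. Both analyses rely on missingness at random given arm and baseline data, so their agreement cannot show how far dropout on unobservables could move the CBCL result. How large such a bias would be cannot be derived from the document.

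Under the assumed 25%/10% loss and the 0.3 to 0.5 SD departures tabulated, the shift is 0.045 to 0.125 SD. It would be tempting to conclude that the planned effect would not survive. That is not supported: an observed 0.53 stays significant throughout that range and is threatened only by heavier loss, larger departures or opposite departures in the two arms. Observed effects up to roughly 0.41 to 0.49 are the ones at risk. This is a worthwhile improvement to the analysis, not a defect that undermines the trial.

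**What to change.** - Keep the planned multiple imputation as the zero-shift case.
- For the CBCL at T2 and T3, add a delta-adjusted (pattern-mixture) analysis. Shift the imputed values separately in the UC and MBT arms over a prespecified range, for example −0.5 to +0.5 SD. Pass each data set through the same stratum-weighted, cluster-robust regression, and report the shifts at which the conclusion changes.
- Report outcome attrition by arm at each time point.
- State that the sensitivity analysis is run whenever outcome data are missing, so that it does not hang on an undefined judgement of what is substantial.
- If a statistical analysis plan already contains such an analysis, refer to it.

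The cost is a few sentences and some extra model runs, with no new data or families. The shift range has to be fixed in advance and is partly a judgement, so its rationale should be given.

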### Interviews and observations

A central component of the MBT model is to enhance reflective capacities in the treatment environment around the foster child to ensure a professional, reflective relationship between foster families and foster care consultants. Therefore, we will apply qualitative methods to examine how reflective processes are implemented in practice. Through interviews and observations, we will examine how the implementation of MBT promotes and facilitates reflective capacities and practices in foster care consultants and in their interactions with foster parents. We will apply a case study design to help us clarify the influence of the context [71]. Data will be collected in four municipalities that differ in critical strategic characteristics (e.g., size, rural/urban). Across the four municipalities, we will look for similarities and differences in the implementation of MBT. Finding regularities across different municipalities will be seen as an indicator of robustness [71].

Data will consist of: (1) video recordings for use in foster care consultant’s supervision, (2) observational data from sessions with foster families and from supervision sessions with MBT supervisors, and (3) semi-structured interviews with foster care consultants. In each municipality, we will collect data from four foster care consultants (two MBT therapists and two control therapists), providing data from 16 foster care consultants in four local contexts.

We will collect video recordings from virtual group supervision sessions (one per group) for MBT therapists. We will conduct two observations and interviews with each MBT and control therapist. Observations and interviews will be conducted in the beginning of the intervention when the focus of intervention is being established and again after four to eight weeks (by the end of the intervention). The observations will be conducted as non-participatory observations based on a semi-structured observational framework [72]. The interviews will be individual and conducted in person.

All interviews and observations will be audio-recorded and transcribed verbatim. Data will be analyzed based on thematic analysis [73] including the following steps: getting familiar with the data and generating initial codes, followed by a process where we search, review and name themes [73]. We expect that themes will include reflective reasoning, changes in the work procedures, and cooperation with foster families. NVivo will be used as analytical software in this process.

## Discussion

This prospective cluster-randomized controlled trial aims to explore the effects of MBT for foster families and foster children aged 4–17 years old in Denmark on measures of child mental health and well-being, foster/parent–child relationship and attachment, as well as foster parent stress and mental health. Furthermore, follow-up measures included in the trial may enable analyses of the effectiveness of the MBT intervention in preventing placement breakdown, which is a known risk factor for long-term positive outcomes for children in foster care. To our knowledge, this is the first randomized controlled study examining the effects of an attachment-based intervention on foster families in the Scandinavian context. This is paradoxical, as the importance of attachment theory within foster care is often seen as taken-for-granted knowledge in official documents and clinical guidelines [17].

In Denmark, there are rather large differences between the municipalities in terms of sociodemography and population size, which results in large differences regarding the number of children placed in care within each municipality. This means that municipalities with relatively many children in care also have a high number of highly skilled foster care consultants, or they may already have psychologists or family therapists who provide therapeutic interventions for foster families in times of high stress. On the other hand, some municipalities with more budgetary restrictions or with very few children in care may only employ a few foster care consultants. Consequently, the practical execution of the study will be streamlined as much as possible but with a high degree of respect for what is actually possible within the participating.

The MBT therapists who receive the training will vary in terms of educational background and clinical experience. This is likely to cause variation in the delivery and receipt of the MBT intervention. The study will provide insight into these differences, as we will be able to conduct moderator analysis based on therapist characteristics.

Other potential limitations relate to methodological as well as practical challenges. A practical challenge concerns the probability of attrition among foster families allocated to the control group. If MBT is perceived as an attractive offer, being assigned to UC while still spending time answering questionnaires and providing a video of foster parent/child interaction to be used for research might be difficult to accept. Because we cannot apply strict random allocation, comparability between the intervention group and control group cannot be guaranteed, and conclusions about causality are expected to be tentative rather than definitive. On the other hand, the study is conducted in a naturalistic setting, which can be regarded as a strength as it increases the ecological validity of our findings and the likelihood that the municipalities may decide to continue to offer the MBT intervention after the end of the trial.

## Data Availability

To protect participant privacy, the datasets generated and analyzed during the current study are not publicly available, but are available from the corresponding author upon reasonable request.
